#### Metabolic measures

We will assess HbA1c using the A1cNow Self Check test (PTS diagnostics). BMI and body fat will be measured using a Tanita scale. We will also collect waist and hip circumference measures. A frequently sampled intravenous glucose tolerance test (FSIGT) will be used to measure insulin sensitivity [18, 19]. Venous samples for plasma glucose and insulin will be drawn at -15, -10, -5, 3, 4, 5, 6, 8, 10, 14, 19, 22, 25, 27, 30, 40, 50, 60, 80, 100, 140, 180 min. Glucose (300 mg/kg) will be injected over 2 min at 0 min. Initially, our protocol stated that insulin (0.02 U/kg) would be infused at the 20-min time point, but the insulin was dropped from the protocol due to hypoglycemia in several of the initial participants. Minimal model analyses will be performed using the Minmod Millennium software [20]) which will provide the insulin sensitivity index (SI), the acute insulin response to glucose (AIRg) and the disposition index (DI = AIRg × SI), a marker of diabetes risk.

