### Data analysis

Data will be analyzed using R (Version 3.2)^61^ All analyses will be performed on an intent-to-treat basis. Significance will be defined p values < 0.05 on two tailed tests.

#### Aim 1

Cross-sectional relationships between circadian alignment, sleep duration and cardiometabolic health.

We will use a multivariable linear regression to model the relationship between insulin sensitivity index at baseline (the outcome) with the baseline circadian alignment, controlling for sex, age, and race/ethnicity. Secondary analyses will be conducted similarly using other measurements at baseline. Other variables, all taken at baseline, being modeled will include metabolic variables – acute glucose response, disposition index, HbA1c, BMI, and body fat – neurobehavioral variables – delay discounting and stop/signal – and behavioral variables – diet quality and physical activity.

In all models, transformation of the outcome will be done if needed for normality. Regression diagnostics will be examined to check for outliers or influential data points as well as for nonlinear relationships with circadian alignment. Additional exploratory analyses will add pairwise interaction terms to evaluate effect modification by sleep duration and sex.

#### Aim 2

We will examine the differences in morning and evening measurements in several outcomes. The primary outcome we will be examining is the calories consumed. Secondary outcomes will be neurobehavioral variables – delay discounting, stop/signal, and processing speed – and mood or hunger rating variables – sleepiness, hunger, and appetite. First, we will use paired t-tests to examine differences for all outcomes. We will then use multivariable linear regression to model the relationship between the difference (morning vs. evening) in calories consumed and DLMO time, controlling for sex, age, and race/ethnicity. Regression diagnostics will be examined for nonlinearity, outliers, and influential data points. For additional outcomes, we will examine similar models.

#### Aim 3

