### Sample size justification

Sample size determinants: We aim to enroll 120 subjects and, accounting for a 20% attrition rate, this will allow us to collect complete data on 96 subjects. Based on standard deviations of 32.1 mg*L^2/(mmol*mU*min) or insulin sensitivity index [33] and 57 min for circadian alignment, we can estimate the minimum detectable effect at 80% power to be 0.161 mg*L^2/(mmol*mU*min) /min for a univariable linear regression. Further assuming a correlation of 0.4 between the covariates and circadian alignment, we can estimate the minimum detectable effect (of circadian alignment on insulin sensitivity index) in the multiple regression to be 0.176 mg*L^2/(mmol*mU*min). We will use all available resources to recruit the planned number of participants, but due to slowdowns and stoppages related to the COVID-19 pandemic, we may not reach the full sample size planned for this study. If we enroll 100 participants rather than 120, it will increase the minimal detectable effect size by 9.5%. If we enroll 110 participants, it will increase the minimal detectable effect size by 4.5%.

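### The FSIGT lost its insulin step after the first participants, but the Aim 1 model for SI has no term for test version and states no other handling

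*Protocol article*

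**What the plan says.** Under Metabolic measures, the protocol article describes two forms of the same test. The first is past: "Initially, our protocol stated that insulin (0.02 U/kg) would be infused at the 20-min time point". The article then says that "the insulin was dropped from the protocol due to hypoglycemia in several of the initial participants". It goes on to describe a single minimal-model analysis that yields SI, the acute insulin response to glucose (AIRg) and DI, the product of the two. It does not distinguish tests done with insulin from tests done without.

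Under Data analysis, Aim 1, the primary regression is to "model the relationship between insulin sensitivity index at baseline (the outcome) with the baseline circadian alignment, controlling for sex, age, and race/ethnicity". DI is among the secondary outcomes, to be modelled in the same way. The opening of Data analysis puts all analyses on an intent-to-treat footing.

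Sample size justification uses one SD for SI. The section on COVID-19 adaptations does not mention the test. Missing data says that imputation models will hold the outcome-model variables plus further variables related to missingness or to the imputed values, but does not name test version.

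**The concern.** SI is estimated from the glucose and insulin curves sampled to 180 minutes. Removing an insulin dose at 20 minutes changes what is observed at every later sample, so the two versions need not give SI with the same mean or spread. DI inherits any difference through SI. AIRg is the response to the glucose given at time 0, before the insulin step, and should be little affected.

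Two things are at stake for the Aim 1 primary result. A difference in level between versions that the model ignores goes into the residual and widens the confidence interval for the slope. And version was not assigned at random: it follows enrolment order. Recruitment began in 2019 and ran into the pandemic, so early and later recruits could differ in sleep timing and alignment. If they do, part of the estimated slope would reflect which test a participant had.

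**Working it through.** **Inputs from the protocol article.** Two-sided 5% level ("Significance will be defined p values < 0.05 on two tailed tests"); 80% power; SD of SI 32.1; SD of alignment 57 min; 120 enrolled less 20% attrition = 96; correlation of 0.4 between covariates and alignment.

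**The plan's own figures.**
- Univariable detectable slope: (1.960 + 0.842) × 32.1 / (57 × √96) = 0.161 per min, as stated ("we can estimate the minimum detectable effect at 80% power to be 0.161").
- Adjusted: 0.161 / √(1 − 0.4²) = 0.176, as stated.
- In SD units: 0.161 × 57 / 32.1 = 0.286 univariable, and 0.286 / √0.84 = 0.312 adjusted. The Aim 1 model is the adjusted one, so 0.312 is the benchmark.

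The sample-size arithmetic is sound. It simply assumes one SD for one test.

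**Inputs that the article does not give (assumed).** f = share tested with insulin, 5–25% (about 5 to 24 of 96). d = shift in mean SI between versions, 0.5–1.0 within-version SD. Alignment difference between early and later recruits, 0.3 SD.

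**Noise.** A level shift that the model ignores adds f(1 − f)d² to the variance, in units of the within-version variance. The standard error is multiplied by √(1 + f(1 − f)d²). Power is evaluated at the planned adjusted slope of 0.176.

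| f | d | added variance | SE increase | power |
|---|---|---|---|---|
| 5% | 0.5 | 0.012 | 0.6% | 79.5% |
| 10% | 0.25 | 0.006 | 0.3% | 79.8% |
| 10% | 0.5 | 0.023 | 1.1% | 79.1% |
| 10% | 1.0 | 0.090 | 4.4% | 76.5% |
| 25% | 1.0 | 0.188 | 9.0% | 72.9% |

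The last power figure is Φ(2.802/1.090 − 1.960) = Φ(0.611). The row with d = 0.25 lies below the assumed range and shows how quickly the cost falls away.

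**Bias.** With version left out, the standardised slope shifts by about f(1 − f) × d × 0.3.
- Low end: 0.0475 × 0.5 × 0.3 = 0.007, or 0.007/0.312 = 2% of the adjusted detectable effect.
- High end: 0.1875 × 1.0 × 0.3 = 0.056, or 0.056/0.312 = 18%.

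This formula ignores how version relates to the other covariates. If version were unrelated to them, dividing by 0.84 would give roughly 3–21%. If version is unrelated to alignment, given the covariates, the bias is zero.

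**Cost of the remedies.**
- Version indicator: for a correlation of 0 to 0.2 between version and alignment, the detectable slope goes from 0.176 to at most 0.176/√(1 − 0.2²) = 0.179, plus about 0.6% for one degree of freedom (√(91/90) = 1.0055).
- Restriction to tests without insulin: 0.176/√0.95 = 0.180 at f = 5%, and 0.176/√0.75 = 0.203 at f = 25%.

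**The case against.** The strongest reply is that pooling is never stated. The article does not say whether the insulin tests were kept, repeated, stopped early or excluded, and after hypoglycemia some may not be usable. The intent-to-treat sentence says little in an observational study without assigned treatment. A condensed article also commonly leaves sensitivity analyses and summaries by test version to a full analysis plan, which is not shown. This stands in part. A reader might infer that the plan declares it will pool the two versions; it does not. Pooling is what follows from one SI, one model, a named covariate list and no exclusion rule. That list is a stated choice and can be judged, whatever an unseen plan may add.

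The second reply is about size. Every input to the magnitude is assumed. Initial participants may mean only a handful, the units of SI are already per unit of insulin, and nothing in the article shows a shift of half an SD or more. This stands in full. At 10% and 0.5 SD, the loss is about one power point.

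The third reply is that bias is conjecture. The article does not say when insulin was dropped, and it reports no difference in alignment between early and later recruits. This also stands: bias is possible, not shown.

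Last, the imputation wording already leaves room for test version as an auxiliary variable. True, but putting it in the imputation model alone leaves the outcome model without it.

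**Conclusion.** The point holds as a gap between a reported change of test and the stated primary model: as written, SI and DI from two versions would be analysed as one measurement. Confidence is high on that and low on the impact. Under the assumed 5–25% share and 0.5–1.0 SD shift, the standard error rises by about 0.6–9%. With a further assumed 0.3 SD difference in alignment, the bias is about 2–18% of the adjusted detectable effect of 0.312 SD per SD. Few insulin tests or a small shift would make both negligible.

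A reader might go further and conclude that the Aim 1 estimate is biased or unusable. The article does not support that, because it gives no count, no shift and no link between version and alignment. This should be fixed because it concerns the primary outcome and the remedy is cheap, not because a large effect has been shown.

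**What to change.** 1. State how many tests were done with insulin and whether their SI values are kept in the analysis.
2. Add a test-version indicator (insulin given: yes/no) to the Aim 1 models with SI or DI as outcome, and name it in the imputation models for both.
3. Pre-specify a sensitivity analysis of SI and DI restricted to tests without insulin. The indicator removes a shift in level only; the restricted analysis also guards against a difference in spread.

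These should be fixed before SI is analysed, so that the choice among pooling, adjusting and excluding does not depend on the results. The cost is one degree of freedom and one extra analysis, provided that it is known for each test whether insulin was given; the article does not say how this is recorded. No change to the test procedure is proposed.

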#### Neurobehavioral testing

The primary neurobehavioral measure will be the 5-trial adjusting delay discounting task [21]. We will also administer measures of inhibitory control (cite stop signal) [22], risk taking using the Balloon Analogue Risk Task (BART Task) [23] and processing speed (digit symbol) [24].

#### Eating behaviors

We will measure hedonic eating using the eating in the absence of hunger task [25], which consists of an oatmeal pre-load followed by a sham taste test. Eating behaviors in daily life will be measured using the Automated Self-Administered 24 h diet recall (ASA 24) [26]. Using values derived from the ASA 24, we will calculate the healthy eating index (HEI) as a composite measure of diet healthfulness [27].

Other self-report questionnaires administered include the PROMIS sleep disturbance measures [28] work hours and conditions [29] and questionnaires to measure perceived stress, demographics and household conditions [30–32].

### Data analysis

Data will be analyzed using R (Version 3.2)^61^ All analyses will be performed on an intent-to-treat basis. Significance will be defined p values < 0.05 on two tailed tests.

#### Aim 1

Cross-sectional relationships between circadian alignment, sleep duration and cardiometabolic health.

We will use a multivariable linear regression to model the relationship between insulin sensitivity index at baseline (the outcome) with the baseline circadian alignment, controlling for sex, age, and race/ethnicity. Secondary analyses will be conducted similarly using other measurements at baseline. Other variables, all taken at baseline, being modeled will include metabolic variables – acute glucose response, disposition index, HbA1c, BMI, and body fat – neurobehavioral variables – delay discounting and stop/signal – and behavioral variables – diet quality and physical activity.

In all models, transformation of the outcome will be done if needed for normality. Regression diagnostics will be examined to check for outliers or influential data points as well as for nonlinear relationships with circadian alignment. Additional exploratory analyses will add pairwise interaction terms to evaluate effect modification by sleep duration and sex.

#### Aim 2

We will examine the differences in morning and evening measurements in several outcomes. The primary outcome we will be examining is the calories consumed. Secondary outcomes will be neurobehavioral variables – delay discounting, stop/signal, and processing speed – and mood or hunger rating variables – sleepiness, hunger, and appetite. First, we will use paired t-tests to examine differences for all outcomes. We will then use multivariable linear regression to model the relationship between the difference (morning vs. evening) in calories consumed and DLMO time, controlling for sex, age, and race/ethnicity. Regression diagnostics will be examined for nonlinearity, outliers, and influential data points. For additional outcomes, we will examine similar models.

#### Aim 3

We will examine longitudinal changes in several outcomes over the course of a year, specifically at three time points – baseline, 6 months, and 12 months – and how they related to circadian alignment at baseline. We will first look at the relationship between our primary outcome, HbA1c, and circadian alignment (at baseline), while adjusting for covariates age at baseline, sex, race/ethnicity and sleep duration. Visit time (baseline, 6 months, and 12 months) will be modeled as a categorical factor and an interaction between visit time and our main predictor, baseline circadian alignment, as well as each of the covariates. We will use a linear mixed effects regression model with an unstructured covariance model to account for serial correlation. If convergence fails, we will compare alternative models for serial correlation, such as heteroscedastic auto-regressive models and compound symmetry, using likelihood tests or AICs to choose the preferred model. A similar procedure will be followed for additional outcomes BMI, body fat, diet and physical activity.

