**Fig. 1 Fig1:**
[figure not shown]
Procedure. * Indicates visits conducted in randomized counterbalanced order. Neuro= neurobehavioral testing, circ= circadian testing, met= metabolic testing

#### Visit 1

Screening/baseline. Participants who are potentially eligible based on the online or telephone prescreening will complete an in-lab screening (visit 1) which involves informed consent, blood draw for HbA1c, height and weight measurement to determine BMI criteria, one night with an Apnea Link monitor (Resmed Inc.) to screen for presence of OSA and 7 days of wrist actigraphy (brand, model) to screen for sleep timing criteria. After reviewing the screening data, research staff will call participants to inform them of their eligibility. Participants who are excluded due to high risk for OSA or diabetes will be provided with a results letter and recommended to discuss with a physician.

#### Visits 2 and 3

These visits will be scheduled in counterbalanced order (Day A and B), with approximately 14 days between sessions, to reduce carryover effects in the neurobehavioral testing. Day A starts at 9 am and consists of neurobehavioral testing in the morning session, questionnaires and free time mid-day (quiet laboratory activities such as watching TV or reading) and circadian phase assessment, (dim light melatonin onset, DLMO), in the evening. Participants will be discharged at their habitual bedtime. For Day B, participants arrive at the University of Utah Center for Clinical and Translational Science outpatient location at 8:30 am. Participants will be instructed to fast for the 8 h prior to their visit. Participants will undergo a frequently sampled IV glucose tolerance test from 9:00 am to approximately 12:30 pm. After this test, participants will go to the behavioral sleep medicine laboratory and will be provided with lunch. The afternoon will consist of completing self-report questionnaires and then participants will have free time for quiet activities in the laboratory. Snacks will be provided ad libitum. The neurobehavioral testing will start at 7:45 pm and discharge will occur around 9:30 pm.

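### Aim 2 compares morning and evening sessions held in randomised counterbalanced order, but the paired t-tests and the DLMO regressions leave visit order out

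*Protocol article*

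**What the plan says.** The Fig. 1 legend marks certain visits with a star: "Indicates visits conducted in randomized counterbalanced order". The paragraph on visits 2 and 3 says "These visits will be scheduled in counterbalanced order (Day A and B), with approximately 14 days between sessions", and gives carryover in the neurobehavioural testing as the reason. The two days carry the two session times. For Day A, "Day A starts at 9 am and consists of neurobehavioral testing in the morning session". For Day B, "The neurobehavioral testing will start at 7:45 pm and discharge will occur around 9:30 pm".

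Aim 2 in the Data analysis section compares morning with evening. On outcomes it says "The primary outcome we will be examining is the calories consumed"; the secondary outcomes are the neurobehavioural tasks and the mood and hunger ratings. The first analysis is: "First, we will use paired t-tests to examine differences for all outcomes". The second is a regression relating "the difference (morning vs. evening) in calories consumed and DLMO time, controlling for sex, age, and race/ethnicity". Order, visit number and sequence do not appear in either analysis.

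**The concern.** Aim 2 is in effect a two-period crossover of session time with randomised order. Repeated delay discounting, stop-signal and processing-speed tasks can plausibly show practice effects. A shift is also possible for the taste test, because participants are no longer naive to it the second time.

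Counterbalancing stops such a shift from biasing the average contrast, but the shift still sits in each participant's difference, with opposite signs in the two orders. An analysis that ignores order counts it as noise. If the numbers completing each order differ, part of it also enters the morning-evening estimate. At stake are power for all Aim 2 outcomes and, under imbalance, the accuracy of the contrast itself.

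**Working it through.** **The plan's own figure.** The Sample size justification sizes Aim 1 only. It reproduces: (1.960 + 0.842) × 32.1 / (57 × √96) = 0.161, and 0.161 / √(1 − 0.4²) = 0.176. No figure is given for Aim 2. From this section I take n = 96 complete participants, and from Data analysis a two-sided 0.05 level.

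**Model.** Let D be morning minus evening, μ the session-time contrast, π the second-minus-first shift, and σ the SD of D within an order. Let p be the share tested in the morning first.
- Morning first: D has mean μ − π.
- Evening first: D has mean μ + π.
- Bias of the unadjusted mean: π(1 − 2p).
- Variance that the paired t-test uses: σ²[1 + 4p(1 − p)(π/σ)²].
- With the order counts fixed, the true sampling SD of the mean is still σ/√96 = 0.102σ.

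**Assumptions.** The article gives neither π nor σ, so π/σ = 0.25, 0.5 and 1.0 is an assumed range. The true contrast is set at 2.802/√96 = 0.286σ, which has 80% power when order is modelled.

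**Equal orders (48/48, p = 0.5).** Bias is 0. In the normal approximation, with r = π/σ, type I error is 2[1 − Φ(1.96√(1 + r²))] and power is Φ(2.802 − 1.96√(1 + r²)).

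| π/σ | Variance used | Type I error | Power, paired t-test | Power, order modelled |
|---|---|---|---|---|
| 0 | ×1.00 | 5.0% | 80% | 80% |
| 0.25 | ×1.06 | 4.3% | 78% | 80% |
| 0.5 | ×1.25 | 2.8% | 73% | 80% |
| 1.0 | ×2.00 | 0.6% | 51% | 80% |

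Simulation with t-tests agrees. At 0.5, for example, type I error was 2.7% to 2.9% and power about 73% across runs. The order-adjusted test stayed near 5% and 80%.

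**Unequal completed orders, π/σ = 0.5.**
- 52/44: the bias is 0.5 × (1 − 2 × 52/96) = −0.042σ. Simulated type I error is about 4%, still below nominal. The test uses an SE of 1.117/√96 = 0.114σ, so it rejects above 1.96 × 0.114 = 0.223σ. Power is Φ((0.286 − 0.042 − 0.223)/0.102) ≈ 58% if the bias opposes the effect, and Φ((0.286 + 0.042 − 0.223)/0.102) ≈ 85% if it adds to it.
- 58/38: the bias is 0.5 × (1 − 2 × 58/96) = −0.104σ. Simulated type I error is about 12%, against 5% with order modelled.

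**How likely is such imbalance?** Suppose 60 per order and 24 lost regardless of order. The completer count in one order then has variance 96 × ¼ × 24/119 = 4.84, SD 2.2, and a 95% range of 44 to 52. A 58/38 split needs 2 losses in one order and 22 in the other. Its chance is about 5 in a million.

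**The case against.** Five points on the other side deserve weight.

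- **No shift is documented.** With π = 0 nothing is lost. The article's remark is "with approximately 14 days between sessions, to reduce carryover effects in the neurobehavioral testing"; it concerns the neurobehavioural tests, and calories, the Aim 2 primary outcome, is not named. This stands. The problem is conditional, and better supported for the secondary outcomes than for the primary one.
- **Bias needs imbalance.** A reader might infer that the morning-evening contrast is materially biased. The documents do not support that. The planned design is balanced, the 20% attrition appears to cover the whole study while these visits are about two weeks apart, and a 58/38 split would need strongly order-dependent dropout. One could argue that the days differ in burden, since Day B includes the glucose tolerance test, but nothing in the article reports dropout by order. The Missing data section also makes multiple imputation the primary approach, though it does not name order in the imputation models.
- **The loss is not a loss of pairs.** A reader might turn a variance factor of 1.25 into 96/1.25 ≈ 77 effective pairs. That is wrong for balanced orders: the true sampling SD stays at 0.102σ, and only the estimated standard error is too large.
- **The DLMO slope.** Randomised order is unrelated to DLMO time in expectation, so leaving it out does not systematically bias the slope. This stands.
- **Condensed article.** A fuller analysis plan might include order. But the article names the test, applies it to every Aim 2 outcome and lists the regression covariates, so this is a stated analysis that does not match the stated design.

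**Conclusion.** The point holds as an efficiency problem, with a smaller and conditional risk of bias. With equal orders the paired t-test is valid and unbiased but conservative. At an assumed shift of 0.5 SD of the difference it gives up about 7 points of power (73% against 80%). The loss is about 2 points at 0.25 SD and 29 points at 1.0 SD. Under imbalance of the size that order-unrelated dropout could produce (up to about 52/44), the bias at 0.5 SD is about 0.04 SD. The figure of 0.10 SD belongs to an extreme case and should be labelled as such. In the DLMO regressions the cost is mainly residual variance.

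These sizes rest on assumed period effects, 96 complete pairs and a true contrast of 0.286 SD. The point does not reach the Aim 1 sizing or the Aim 1 models.

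**What to change.** Replace the Aim 2 paired t-test with a regression of the within-person difference on order coded +1/−1; the intercept is then the session-time contrast adjusted for period. An equivalent choice is a mixed model with session time, visit number and a random participant effect. Add the same order term to the regressions of the difference on DLMO time.

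The cost is one degree of freedom and a change of wording, with no new data. If there is no period effect, almost no power is lost.

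The plan should also state the limits of the term. It does not remove carryover that differs by sequence. Nor does it separate time of day from whatever else differs between the days, such as the glucose test, lunch and snacks that precede evening testing on Day B.
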